### Sample size

The results of a pilot study conducted on 30 participants prior to the main study showed that the combined NLP and machine learning had an accuracy of 72–80% for binary classification to differentiate between disease and healthy controls (based on a leave-one-out cross-validation). The demographic data in the pilot study are as follows. Age (years, mean ± SD): 56.8 ± 16.9, Gender (%male): 46.7, Diagnosis: 5 schizophrenia, 1 bipolar disorder, 4 depression, 5 anxiety disorder, 5 neurocognitive disorder, and 10 healthy controls.

Specifically, we used the part of speech information as well as feature vectors extracted from the data points using an NLP package called SpaCy as the input to train an XGBoost model for predicting the labels of the data points. We cross-validated the XGBoost model using leave-one-out cross-validation (LOOCV) where we would leave one data point as the test data and train an XGBoost model using the remaining data points. The process repeated for each data point and computed the accuracy of the LOOCV as the ratio of correctly predicted data points out of all of the data points. We further optimized the hyperparameters of the XGBoost model by choosing the set of parameters that has the highest LOOCV accuracy.

We constructed a learning curve to estimate the number of samples required to achieve a classification accuracy of 90%. Starting from a sample size of 15, we randomly sample 15 data points from the total of 30 data points and perform the LOOCV as described above, and repeat the random sampling of 15 data points 10 times, each time keeping track the optimal classification accuracy to get an idea of the distribution of the accuracy for 15 data points.

We then repeat the whole process at one-sample increments until we reach 29 samples. The resulting accuracies are then fitted to a linear model. Based on the parameters of the fitted linear model, we estimated the number of data points required to achieve an accuracy of 90%.

We calculated that a minimum of 50 samples would be required. In addition, considering the variability of the data over a wide range of age groups, severity of illness, and regional differences, it was estimated that about 10 times the number of samples would be necessary. Another means of approximating sample sizes for regression analysis is that the number of cases should be approximately 10 times the number of the independent variables used to obtain statistical confidence (48).

In the pilot study, we used 62-dimensional features for speech information and linguistic information. These features include linguistic features such as the number of morphemes, the number of vocabulary, the number of nouns, verbs, and adjectives, the number of particles “ga” etc., and the number of conjunction, and non-linguistic features such as the total time, the response time, the number of fillers, the formants. In the present study, we plan to use a total of about 100 independent variables for the analysis. We will also be employing dimension reduction and feature selection techniques to reduce the number of independent variables in the model. Based on the approximations, we estimate that the desired sample size is approximately 1,000. It should also be noted that the actual needed number of samples is likely to be lower.

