The present study aims to create large datasets of the Japanese language with a great number of samples, types, and amount of utterances and look into ways to extract linguistic and audio indicators that can be used to differentiate between healthy-disease and disease-disease. Such datasets are limited at present (38). They could enable us to obtain reliable results and bring pioneering insights from NLP in the Japanese-speaking region. Notably, this study aims to target 300–500 participants and obtain 600–2,500 corpora; as such, it will be one of the largest participants' records among studies examining the diagnosis of major psychiatric disorders using NLP. This research also aims to deepen our understanding of the characteristics of psychiatric disorders and quantify them using NLP and machine learning so that the features of psychiatric disorders can be identified and quantified in the future. Such technology could eventually be used for early diagnosis and prevention.

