In this study, not only the collection of linguistic information associated with each disease but also the relationship between illness severity and linguistic information will be important. Therefore, we will follow the participants two to five times during the study period to interview the subjects at times when the severities of their symptoms differ (i.e., severe, moderate, mild, and during remittance). An interval of at least 1 month between the two assessments will be required. The same procedures described above will be conducted for the follow-up data collection.

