### Machine learning

The machine learning models in this study will be trained to perform the following tasks: (1) to predict whether a subject has or does not have psychiatric disorders such as depression, bipolar disorder, anxiety disorder, schizophrenia, or dementia; (2) to predict the severity of a subject's state based on the results of rating scales such as the Hamilton Rating Scale for Depression (HAM-D), the Young Mania Rating Scale (YMRS) for bipolar disorder, the Positive And Negative Syndrome Scale (PANSS) for schizophrenia, and MMSE for dementia; (3) to predict the improvement or deterioration of a subject's disorder with respect to a previously recorded state if the subject has undergone a prior assessment; and 4) to predict the scores of individual items in clinical rating scales that are indicators of different aspects of a subject's disorder, such as positive symptoms, negative symptoms, and disorganized symptoms for schizophrenia. The data used to train these machine learning models may include voice features extracted from voice data obtained from subjects, conversational and linguistic information from transcribed text data, and annotations assigned to the data described above.

Next, we will need to perform feature engineering and design the architecture of machine learning. The data, represented through NLP techniques, together with the features obtained through feature engineering processes, will be then used to extract disease features. In particular, disease features extraction will be performed relying on machine learning models such as decision trees, support vector machines (SVM), and deep learning architectures. Each model will be evaluated using cross-validation and then the relative importance of each feature will be estimated using a feature importance estimation method such as XGBoost. We will then evaluate the results using the mean absolute error, coefficient of determination, and correlation coefficients. We also plan to verify whether the features obtained in this manner can distinguish firstly between a normal and disease state, secondly among different diseases, and whether they can distinguish changes in disease severity over time.

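### Cross-validation is the only model evaluation named, yet nothing keeps a participant's repeat records in one fold, and the plan counts records as samples

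*Protocol article*

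**What the plan says.** **Evaluation.** The Machine learning section states: "Each model will be evaluated using cross-validation and then the relative importance of each feature will be estimated". It names no fold type, no splitting unit and no held-out or external test set.

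**Repeat records.** After Table 1 the article says "we will follow the participants two to five times during the study period". The Introduction plans 300–500 participants and intends to "obtain 600–2,500 corpora". The Discussion reports more than 1,000 datasets from more than 400 participants by September 2022.

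**What counts as a sample.** The Sample size section applies a rule of about 10 cases per independent variable, expects about 100 variables, and arrives at a desired sample size of about 1,000.

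**The only cross-validation described.** This is the pilot's leave-one-out procedure in the Sample size section, "where we would leave one data point as the test data and train an XGBoost model using the remaining data points". For the pilot learning curve, "we randomly sample 15 data points from the total of 30 data points".

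**Inputs and label.** The extracted voice features include fundamental frequency, formants and mel-frequency cepstrum coefficients. Each visit repeats the same procedures, with the same pictures and story task. Diagnosis is listed among the demographic characteristics, which Table 1 schedules at visit 1 only.

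**The concern.** Records from one person are not independent. A speaker's pitch, formants, vocabulary and style persist from visit to visit, and so does the diagnosis. If folds are formed from records, most test records have a sibling in the training set that carries the right answer. A flexible model can then do well by recognising the speaker, and the resulting accuracy says little about a patient it has never heard.

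The stated aim is a biomarker for diagnosis, which means use in new people. Cross-validation is the only evaluation named, so nothing later in the article would expose this inflation. For Task 1 the bias runs upward.

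The article gives no unit other than the data point or record, and it sizes the study in that unit. A team that followed the text literally would run the leaking analysis.

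**Working it through.** **1. The pilot, where the described scheme is safe.** The article reports "The results of a pilot study conducted on 30 participants prior to the main study", and the diagnoses are "5 schizophrenia, 1 bipolar disorder, 4 depression, 5 anxiety disorder, 5 neurocognitive disorder, and 10 healthy controls".

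- Persons: 5 + 1 + 4 + 5 + 5 + 10 = 30.
- Data points: 30, so 30 / 30 = 1 per person.

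Leaving out a data point was therefore leaving out a person. The finding that the classifier "had an accuracy of 72–80% for binary classification to differentiate between disease and healthy controls" is not affected by same-person leakage.

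**2. The plan's own figures reproduce.**

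- Corpora: 300 × 2 = 600 and 500 × 5 = 2,500, as stated.
- Desired sample: 10 × 100 = 1,000, as stated.

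**3. What the 1,000 must be.** With at most 500 participants, 1,000 samples need 1,000 / 500 = 2 records each; with 300 participants, 1,000 / 300 = 3.3 each. The target is reachable only if repeat records of one person count as separate samples. Collection so far is about 1,000 / 400 = 2.5 records per participant.

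**4. Size of the leak if folds were split by record.** This was simulated with no diagnostic signal.

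- Model: feature = person effect (variance ICC) + visit noise (variance 1 − ICC), with 100 features. The label is fixed per person and unrelated to any feature.
- The intraclass correlation (ICC) is an **assumption**, because the article gives none. The range shown is 0.3–0.7 for all features.
- The correct answer is 50%.

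| Setting | Classifier | Record-level folds, ICC 0.3 / 0.5 / 0.7 | Participant-grouped folds |
|---|---|---|---|
| 102 vs 89 persons, 2–3 records, 10-fold | RBF kernel | 62 / 77 / 94% (repeat run 63 / 78 / 93%) | 49–51% |
| 35 vs 58 persons, 10-fold | RBF kernel | 62 / 79 / 94% | 48–50% |
| 102 vs 89 persons, 2–3 records, 10-fold | linear | 57–66% over the range | 50–52% |
| 300–500 persons, 2–5 records, 10-fold | linear ridge | 54–62% over the range | 49–50% |
| 300–500 persons, 2–5 records, leave-one-out | nearest neighbour | 66–77% / 98–100% / 100% | 48–51% |

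The group sizes 102, 89, 35 and 58 are the article's counts for schizophrenia, depression, anxiety disorder and bipolar disorder. The first two rows and the third are balanced accuracy; the last two use equal classes. At an assumed ICC of 0.1 the RBF figure falls to 54%. Nearest neighbour is not a method the article names; it marks the extreme in which the model simply looks up the speaker. Tree-based and deep models were not simulated.

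**5. Which tasks are exposed.** Task 1 predicts diagnosis, which stays constant across a person's records. Tasks 2–4 predict severity, change and item scores, and the article schedules visits at differing severities. Identity is a weaker guide to those labels. Only Task 1 was simulated.

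**The case against.** The strongest objection is that the article never says the main study will split by record. The leave-one-out sentence is in the past tense and reports a finished pilot with one record per person. The Machine learning section is silent on the splitting unit, words Task 1 in terms of a subject, and says the architecture still has to be designed. A condensed article may leave fold construction to the full protocol or analysis plan.

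Much of this stands. A reader might infer that the pilot accuracy is contaminated by repeat records; it is not, since 30 data points were 30 people. A reader might also infer that record-level folds are the stated main-study plan; no passage says so.

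It does not dispose of the point. The article sizes the study in records, describes its one cross-validation procedure step by step in data points, and names no other evaluation. The independent unit is what makes that sole evaluation valid, and the only unit the text supplies is wrong for repeat visits.

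A second objection is that the simulated inflation rests on assumed correlations, on the classifier, and on using all 100 features although dimension reduction and feature selection are planned. That is fair. It limits what can be said about size, not about direction. It also rules out saying without conditions that 90% can be passed on noise. In these runs that happened only with flexible classifiers at the higher correlations: RBF at 0.7, nearest neighbour from 0.5. Moreover, the article uses 90% as a target for the pilot learning curve, not as a success criterion for the main study.

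**Conclusion.** The point holds as a gap that the plan's own choices make hazardous; it is not an error already committed. The article relies on cross-validation alone, counts repeat records as samples, and offers only a data-point split as a model. Carried over to two to five records per person, that split would bias Task 1 accuracy upward.

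With no true signal, the inflated figure is about 54–66% for linear classifiers and about 62–94% for an RBF classifier, against about 50% with grouped folds. This assumes within-person correlations of 0.3–0.7, a diagnosis that does not change between visits, and record-level folds. If the correlation is near 0.1, or the unpublished plan already groups by participant, the effect is small or absent. Tasks 2–4 are less exposed, by an amount not estimated here.

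**What to change.** Add to the Machine learning section that all records of a participant are kept in the same fold for every task, and that the same rule applies to the folds used for tuning and feature selection. Tuning needs naming because the pilot chose its hyperparameters by leave-one-out accuracy. State also that confidence intervals, if reported, are obtained by resampling participants rather than records.

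The cost is a sentence or two in the plan and a grouping variable in the code; the study number already identifies each participant. No new data are needed. The downside is that reported accuracy may be lower. If the full protocol already groups by participant, a line saying so settles the matter.

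A leave-one-site-out run across the ten recruiting sites would be a useful extra, but it is optional and not part of this correction.

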#### Data processing and annotation

The acquired voice data will be converted into text information using speech recognition technology developed by the research group and will be compensated manually; annotations, such as pauses, fillers, nods, interjections, repetitions, co-supplementation, lexical responses, incomplete sentences, misstatements, etc., will also be made. We will mask the part of personal identifiers such as names when converting voice data into text information. At the same time, the following phonic information will be extracted from the recorded audio data to utilize the physical properties of the audio data in the machine learning model: fundamental frequency (F0); first, second, and third formant frequencies (F1, F2, F3); cepstral peak prominence (CPP); and Mel-frequency cepstrum coefficients (MFCC). These are the major features in speech-language analysis (40). Software such as Praat (41) and openSMILE (42) will be used to extract such phonic information.

Based on the annotated text data thus obtained, various variables are calculated using NLP techniques, such as morphological and syntactic analyses using MeCab (43, 44) and JUMAN (45, 46). For instance, these analyses will include the frequency of the occurrence of each part of speech, vocabulary (negative and positive words), syntactic complexity, length of the utterance, frequency of occurrence of person, use of pronouns and distance to the referent, use of case structure (“te, ni, wo, ha”), and so on. We will use NLP techniques to represent textual data as n-grams and word embeddings obtained from pre-trained models such as BERT (47).

Linguistic features considered to be characteristic of specific psychiatric diseases will be selected and statistically compared between groups (e.g., patients vs. healthy subjects, patients in different disease groups). This step is necessary to verify whether each variable has pathological validity before using it for machine learning.

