## Discussion

The UNDERPIN study is unique in its purpose, the novelty of its methods, such as the use of NLP, and the size of the data sample. It has a broad and evolving perspective that is expected to shed light on traditional psychiatry by applying the new analytical method of machine learning to language. In addition, the large and Japanese-language datasets enhance the novelty. As of September 2022, we have collected a total of >1,000 datasets from >400 participants (102 patients diagnosed with schizophrenia, 89 with depression, 58 with bipolar disorder, 35 with anxiety disorder, and 79 with neurocognitive disorder). The large datasets to be created in this study have the potential of leading to the development of new biomarkers.

Psychiatrists have long relied on language and superficial behavioral data to diagnose psychiatric disorders. Although many empirical studies have explored biomarkers of mental illness (49, 50), no robust biomarkers have been identified that are clinically practicable.

This study will focus on the linguistic features of psychiatric disorders, which have been explored using traditional disciplines such as linguistics (51, 52) and psychopathology. By introducing the method of NLP, we will be able to bring an empirical and mathematical perspective to humanistic examinations. Quantifying linguistic features will allow a more detailed examination of their correlation with other objective measures, such as brain imaging studies. Boer et al. identified features that distinguish patients with schizophrenia and healthy subjects based on speech data; using the calculated features, they then predicted the integrity of the white matter language tracts in two groups (53). Although such studies remain rare (54), they may bring clinical practice and research on psychiatric disorders, which have been suggested to be divergent, closer together.

Moreover, the results of this study could lead to early detection and early intervention for patients with psychiatric disorders. As the concept of duration of untreated psychosis (DUP) suggests (55), early detection and intervention are essential for a favorable disease prognosis.

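### The sample size of about 1,000 has no stated unit; in participants, the study reaches only 3–5 per variable against the cited 10

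*Protocol article*

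**What the plan says.** The Sample size section gives two approximations. The first extrapolates a pilot learning curve to a minimum of 50 samples and multiplies by about 10 to allow for heterogeneity. The second is a rule for regression, under which "the number of cases should be approximately 10 times the number of the independent variables used to obtain statistical confidence". The article then states that "we plan to use a total of about 100 independent variables for the analysis" and concludes: "Based on the approximations, we estimate that the desired sample size is approximately 1,000". It adds that dimension reduction and feature selection will be applied and that the true requirement is probably smaller. It gives no reduced number of variables.

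The Introduction says that "this study aims to target 300–500 participants and obtain 600–2,500 corpora". The Clinical assessment section plans two to five interviews per person, at least a month apart. The Discussion reports, as of September 2022, that "we have collected a total of >1,000 datasets from >400 participants". It lists 102 patients with schizophrenia, 89 with depression, 58 with bipolar disorder, 35 with anxiety disorder and 79 with neurocognitive disorder.

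**The concern.** The words for cases and samples are never tied to a unit. In the pilot, 30 participants supplied 30 data points, so a sample there is a person. In the main study the required number is twice the largest participant target, so the unit appears to have changed to the recording without this being said.

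The change matters because a rule of cases per variable presumes independent cases. Repeat recordings share a speaker, and for the diagnosis task they also share the label. The required 1,000 and the reported count of more than 1,000 datasets look like a match. A reader could take the requirement as met when, counted in people, the study has less than half of it or at most half.

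**Working it through.** **The article's own figure.** 10 cases × 100 variables = 1,000, which reproduces. The learning-curve route gives 50 × 10 = 500, and the 62 pilot features would give 62 × 10 = 620. Only the rule applied to 100 variables yields 1,000.

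**In participants** (targets from the Introduction; 400 is the reported accrual, an open-ended figure):

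| Participants | Per variable at 100 | Below 1,000 by | Variables supported at 10 each | Recordings each needed for 1,000 |
|---|---|---|---|---|
| 300 | 3 | 70% | 30 | 3.3 |
| 400 | 4 | 60% | 40 | 2.5 |
| 500 | 5 | 50% | 50 | 2.0 |

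**In recordings.** The targets are 300 × 2 = 600 to 500 × 5 = 2,500. The lower end misses 1,000 before any allowance for correlation.

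**Effective number for the diagnosis task.** With R recordings, m per person and within-person correlation ρ, the effective number is R / (1 + (m − 1)ρ). The article gives no ρ, so a wide range is assumed:

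| Scenario | ρ = 0.1 | 0.3 | 0.5 | 0.7 | 0.9 |
|---|---|---|---|---|---|
| 400 people, 1,000 recordings (m = 2.5) | 870 | 690 | 571 | 488 | 426 |
| 300 people, 600 recordings (m = 2) | 545 | 462 | 400 | 353 | 316 |
| 500 people, 2,500 recordings (m = 5) | 1,786 | 1,136 | 833 | 658 | 543 |

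For example, 1,000 / (1 + 1.5 × 0.5) = 571. The first scenario equals 1,000 only at ρ = 0. The maximum plan stays above 1,000 while 2,500 / (1 + 4ρ) > 1,000, that is, while ρ < 0.375.

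**Severity models** (interim counts from the Discussion; scales from Table 1; five recordings each as the ceiling). Table 1 gives HAM-D and YMRS to depression, bipolar and anxiety patients alike, so these groups can be pooled:

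| Scale | Patients | Per variable at 100 | Recordings at most |
|---|---|---|---|
| HAM-D, YMRS | 89 + 58 + 35 = 182 | 1.8 | 910 |
| PANSS | 102 | 1.0 | 510 |
| MMSE | 79 | 0.8 | 395 |

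Healthy volunteers complete all scales and could be added. The listed patients sum to 363, so if the total were exactly 400 there would be 37 volunteers. That gives 182 + 37 = 219 people (2.2 per variable), 102 + 37 = 139 (1.4) and 79 + 37 = 116 (1.2). At five recordings each these are 1,095, 695 and 580. Only the pooled mood and anxiety model could then pass 1,000, and only with every person at the maximum number of visits and every recording counted as independent.

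**The case against.** Several points on the other side stand.

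- The wording is cautious: the number is desired and approximate, and the article never says that 1,000 recordings satisfy it. The other approximation, 500, is met in participants at the top of the target range. But the article does not reconcile 500 with 1,000, and the second figure is the one it concludes with.
- The design effect fits a label that is fixed within a person. For severity, interviews are deliberately placed at times of differing symptom level, so repeats carry more information. For predicting change, repeat visits are the data and the formula does not apply. The effective numbers above are therefore claimed for diagnosis only.
- Dimension reduction could bring the variables down to what the participants support. That is correct, but no number is fixed, and the 1,000 was computed from 100.
- The September 2022 counts are interim. The target of at most 500 participants, however, limits every model.
- A regression rule may suit trees, support vector machines or deep learning poorly. It is still the rule the article chose to justify its size.

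A reader might infer more than the documents support:

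- **One diagnosis per severity model**, with 35–102 participants and anxiety as the worst case. Table 1 allows pooling and the addition of volunteers, and the Machine learning section names no anxiety severity scale.
- **Text representations left out of the 100 variables.** The article says "We will use NLP techniques to represent textual data as n-grams and word embeddings obtained from pre-trained models such as BERT", but nowhere says whether these dimensions are inside or outside the count.
- **The remark that fewer samples may suffice is simply wrong.** It would be wrong if variables were chosen using the outcome, since discarded candidates still count. The article does not say how selection will be done, and reduction blind to the outcome would indeed lower the requirement.

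**Conclusion.** The point holds. The multiplication is right, but the result is not a size that the design delivers in independent cases. In participants the study has 3–5 per variable against the cited 10, a shortfall of 50–70%, and this needs no assumption beyond the article's own figures. That the 1,000 counts recordings is an inference, but no other unit fits a ceiling of 500 participants.

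How much repeat recordings recover depends on a correlation that the article does not give. For diagnosis, at the reported accrual, the effective number is about 870–426 over 0.1–0.9. Only a plan near the maximum number of visits, with a correlation below about 0.375, would exceed 1,000. At 100 variables the severity models have about 0.8–1.8 patients per variable on interim counts, or about 1.2–2.2 with the assumed 37 volunteers. The documents do not show that these models will fail; they show that the stated rule does not support them at the stated number of inputs.

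**What to change.** - Define the sampling unit in the Sample size section, and reconcile 500 and 1,000 with the targets of 300–500 participants and 600–2,500 corpora.
- State the size in participants for each model, or as an effective number with a stated within-person correlation and number of visits.
- Replace the figure of about 100 variables by the number of model inputs that the participants support under the cited rule: about 30–50 for the pooled diagnosis model, and correspondingly fewer for each severity scale. Reach it by dimension reduction that does not use the outcome, or use penalised models. Count any n-gram or embedding dimensions that enter a model.
- Limit the remark that fewer samples may be needed to reduction made without using the outcome.

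The cost is rewording and a smaller, prespecified feature set. The size of the study will look less favourable on paper. No extra recruitment is needed.
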